#### Subgroup analyses

We will conduct a comprehensive subgroup analysis to explore potential moderating and mediating effects based on participant characteristics. The subgroup analysis will encompass sociodemographic characteristics (age above or below 55 years, gender, and marital status), ethnicity, socioeconomic status (occupation and related variables), education level, PRS levels (high, intermediate, normal), lifestyle category at baseline (favorable, intermediate, or unfavorable), attitudes toward the use of digital technologies (present/absent), knowledge toward CVDs (present/absent), and psychological status at baseline. The primary objective of this subgroup analysis is to investigate whether the efficacy of the interventions varies across these identified participant subgroups. We aim to understand how sociodemographic factors, genetics, and baseline lifestyle categories may moderate or mediate the effects of the interventions on behavior change and modification of CVD risk profiles.

Statistical analyses will be conducted using STATA (StataCorp, USA) and R (https://www.r-project.org/).

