## Objectives

We will evaluate whether the use of innovative technologies to gather information on lifestyle and genetic determinants in the primary prevention setting can lead to changes in individuals' behaviors and CVD risk. The primary objective is to assess the efficacy of providing CVD polygenic risk score (CVD PRS) information, measured at baseline, either alone or in combination with the use of an app and a smart band (digital technology), on two endpoints: (i) changes in lifestyle patterns, and (ii) modification in CVD risk profiles. The potential lifestyle modification will also be evaluated in relation to other factors such as psychological status, knowledge and attitudes toward CVDs and personalized medicine, and acceptance of wearable devices, which can influence citizens' behavior.

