## Participants, study setting and recruitment

### Participants, inclusion and exclusion criteria

The study will include individuals between the ages of 40 and 69 years who do not have established CVDs, diabetes mellitus, or familial hypercholesterolemia. These individuals should have a high 10-year CVD risk ranging from 2.5 to 10% based on the SCORE 2 charts (12).

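### The exploratory subgroup analysis cuts age at 55 although age in years is available; if moderation is roughly linear, this loses about a quarter of the information on a treatment-by-age interaction, or a third or more if ages are bell-shaped

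*Protocol article*

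**What the plan says.** The Subgroup analyses section of the protocol article opens as an exploration: "We will conduct a comprehensive subgroup analysis to explore potential moderating and mediating effects based on participant characteristics". It then lists the characteristics. For age the scale is fixed by "sociodemographic characteristics (age above or below 55 years, gender, and marital status". Two questionnaire variables are also given as binary: "attitudes toward the use of digital technologies (present/absent), knowledge toward CVDs (present/absent". The stated purpose is interaction: "The primary objective of this subgroup analysis is to investigate whether the efficacy of the interventions varies across these identified participant subgroups".

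The section gives no reason for the cut at 55 and mentions no analysis of age on its own scale. The eligibility section sets the range: "The study will include individuals between the ages of 40 and 69 years". Study procedure names age as one of the variables that enter SCORE 2, so age should be to hand for every participant. The same section places all questionnaires in Appendix 1, which is not shown. Objectives adds, for the questionnaire variables but not for age: "The potential lifestyle modification will also be evaluated in relation to other factors such as psychological status, knowledge and attitudes toward CVDs and personalized medicine".

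**The concern.** Cutting a measured moderator into two groups treats ages 40 and 54 as alike and ages 54 and 56 as different. If the effect of an intervention rises or falls gradually with age, the two-group contrast estimates that gradient less precisely than age in years does. Interaction tests usually have low power already, so a real gradient becomes more likely to be reported as no difference between subgroups.

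A smaller defect needs no assumption. Read literally, a group above 55 and a group below 55 leave participants aged exactly 55 in neither.

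At stake is the sensitivity of one exploratory analysis. The trial's main comparison of arms does not depend on it.

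**Working it through.** **The plan's own figures.** The article gives no figure for information lost in the subgroup analysis. Its sample size can be approximated without any age split. A four-group chi-squared test (3 degrees of freedom, level 0.05) on 5, 8, 10 and 15% needs 177 per arm for 80% power. Allowing for 30% withdrawal, 177/0.70 = 253 per arm and 4 × 253 = 1,012, within 1% of the stated 1,020. The point below does not touch that target.

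**Formula.** For a linear treatment-by-age interaction, the share of information kept by a binary version of age is the squared correlation between age and the indicator:

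share kept = p(1 − p) × (difference between group mean ages)² / variance of age,

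where p is the proportion in the older group.

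**Uniform ages (assumption; the article gives only the range).** For whole years 40 to 69 with 55 in the older group, p = 15/30 = 0.5. The group means are 62 and 47, a difference of 15. The variance is (30² − 1)/12 = 74.92. The share kept is 0.25 × 225/74.92 = 0.751. With 55 in the younger group, p = 14/30 and the share is 0.748. The loss is therefore about 25% either way.

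**Other age distributions (all assumptions), linear moderation:**

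| Age distribution over 40–69 | Information lost |
|---|---|
| Uniform | 25% |
| Weighted linearly towards older ages, 1:2 and 1:4 | 26%, 28% |
| Truncated normal, mean 55, SD 6 to 8 | 32–35% |
| Truncated normal, mean 58 to 60, SD 6 to 8 | 33–45% |
| Mildly U-shaped | 21% |
| Strongly bimodal (peaks at 45 and 65, SD 3) | 7% |

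If the effect is a true step at 55, the cut loses nothing.

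**What a 25% loss means.** Keeping 75% is equivalent to needing 1/0.75 = 1.33 times the sample for the same interaction power. A test with 80% power using age in years falls to 68% with the split.

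**Illustration on LDL cholesterol.** The SD of 15 mg/dL, 255 per arm and 30% withdrawal come from Sample size estimation; 255 × 0.70 gives 178 evaluable per arm. Assumptions: two-sided level 0.05, uniform ages, and one arm-versus-A effect running linearly from 0 at age 40 to 10 mg/dL at age 69, which averages to the plan's 5 mg/dL.

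- Slope = 10/29 = 0.345 mg/dL per year; SD of age = √74.92 = 8.66.
- z with age in years = 0.345 × 8.66 / (15 × √(2/178)) = 2.98/1.59 = 1.88; power 47%.
- z with the split = 1.88 × √0.751 = 1.63; power 37%.

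The gain from age in years is about 10 percentage points. If the effect varies by 5, 7.5, 12.5 or 15 mg/dL over the age range, the gain is 3, 6, 12 or 12 points.

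**Knowledge and digital attitudes.** The source scales are unknown, so only a range can be shown. A yes/no item loses 0%. A scale with equally filled levels, cut at its best point, loses 20% with 4 levels and 25% with 5 or 11. A sum of 2 to 20 binary items, each equally likely to be answered either way, loses 25 to 36% at its best cut. A roughly normal score loses 36% when split 50:50 and 51% when split 20:80. The documents do not say which applies.

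**The case against.** The strongest reply is that a prespecified two-group contrast is a legitimate choice. It prevents a data-driven cut, 55 lies close to the middle of the range (54.5), and the result is easy to report. It also assumes no linearity: if the effect steps at 55, the split is fully efficient and it is the linear term that keeps only about 75%. This stands as a reason not to rely on a straight line alone. It does not defeat a proposal that adds a spline check and retains the two-group table.

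A second reply is that the article is condensed, lists subgroups rather than models, and nowhere excludes age in years. An unseen analysis plan may contain such a term. That is fair, but the one scale the article states for age is the cut.

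A third reply is that the gain is modest. In the LDL illustration both approaches miss the assumed gradient more often than not, the gradient is invented, and LDL is a secondary outcome. This stands too: the change improves a weak test but does not make it strong.

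A reader might also infer that all three variables lose at least a quarter of their information. The documents do not support this. Knowledge and attitudes may be single yes/no items, and even for age a quarter is not a strict minimum. Nor is moderation the trial's main question: Objectives makes the efficacy of polygenic risk information the primary objective. The gap in earlier studies that the Discussion describes concerns mediators, and age cannot be a mediator of a randomised intervention.

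**Conclusion.** The point holds for age, as a minor and nearly cost-free improvement to an exploratory analysis. The loss is about 25% if ages are uniform over 40 to 69 and about a third or more if they are bell-shaped, in both cases assuming roughly linear moderation. It is smaller for bimodal ages and zero for a true step at 55. For knowledge and digital attitudes no loss can be claimed, only that one would arise if a graded score is being reduced to two levels. The handling of participants aged exactly 55 is a loose wording that should be tidied. The primary analysis and the sample size stand as they are.

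**What to change.** In Subgroup analyses, state that effect modification by age is tested as a treatment-by-age interaction with age in years, linear, with a spline as a check on shape. For knowledge and digital attitudes, use the questionnaire score where the instrument has more than two levels, and leave them binary where it does not. Keep the age split for displaying subgroup estimates, defined as under 55 versus 55 and over, so that every participant belongs to a group.

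The cost is wording: no further data, visits or participants are needed. The downside is that a slope, or predicted effects at chosen ages, must be reported beside the two-group table.

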### Genetic testing

Participants assigned to the groups B and D will undergo genetic testing to evaluate their CVD genetic risk profile using a commercially available genome-wide PRS. At the time of enrollment, participants will receive a salivary swab to obtain genomic DNA for analysis. The PRS analysis will be conducted using the Illumina microarray technology, which is a cost-effective genotyping approach for disease and population genetics studies (17). Microarray analysis will generate data on millions of genetic variants per individual, and any gaps between these variants will be filled using imputation analysis. The imputation process compares the sequencing results with a reference dataset, leveraging reference genomes from the 1,000 Genomes Project (18). A modified version of the GLIMPSE algorithm will be utilized for imputing genomic data (19). Based on the combined results, individuals will be classified into three main genetic risk categories for CVD: High risk, Intermediate risk, and Normal risk.

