The cardiovascular evaluation will include measurements of blood pressure, heart rate, objective examination and cardiovascular risk assessment using SCORE 2 charts, incorporating essential variables such as age, gender, systolic blood pressure, total cholesterol, HDL cholesterol, and smoking status (12). Blood analysis will also be conducted, assessing parameters such as total cholesterol, HDL and LDL cholesterol, triglycerides, high sensitivity C-Reactive Protein (CRP), glycated hemoglobin, and/or glycemia.

Participants in Groups B and D will also undergo a salivary swab for PRS analysis.

Subsequently, participants will have a disclosure visit (T1) after 1 month, a follow-up visit (T2) after 5 months, and a final follow-up visit (T3) at 12 months.

During the disclosure visit (T1), participants in all groups will receive an explanation of their lifestyle pattern and cardiovascular risk profile based on SCORE 2 charts, along with written preventive advice for risk reduction and lifestyle changes. Participants in the digital intervention groups (C, D) will also receive an app and a smart band to monitor various health data. A comprehensive demonstration during smart band delivery, along with written instructions on its usage, will be provided to ensure participants consistently utilize the smart band throughout the study, with the recommendation for daily application (24–26). Participants in the PRS groups (B, D) will receive the disclosure of their genetic CVD risk profile.

At both follow-up visits (T2, T3), the comprehensive questionnaire will be administered again to assess changes in lifestyles and psychological status. Any challenges with smart band usage will also be identified. At the final visit (T3), the cardiovascular risk profile will be recalculated, and participants will undergo a final full assessment, evaluation of the lifestyle category, and blood test to evaluate changes in cholesterol levels and other parameters.

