#### Statistical methods for primary and secondary outcomes

The primary analysis will be based on the intention-to-treat principle, where all randomized participants will be analyzed according to their allocated study arm. Baseline characteristics of the four arms will be summarized using descriptive statistics. The baseline characteristics of those who withdraw will be assessed against those who remain in the study.

Groups D, C, and B will be compared with group A to evaluate the marginal effect of adding at least one intervention or both. The analysis will employ adjusted mixed-effect models for repeated measures to assess significant differences in lifestyle patterns, lipid, and CVD risk profiles from baseline to the various follow-up time points (T).

Furthermore, an analysis of the primary outcome will be conducted in a per-protocol fashion to account for non-compliance with uptake of the CVD PRS or use of the app/smart band evaluated at T2 and T3, as well as missed appointments for the complete CVD risk result, as prescribed by their allocated intervention.

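### PRS level is listed as a subgroup for intervention efficacy, but it is measured only in arms B and D, so no stated contrast can be estimated within PRS level

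*Protocol article*

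**What the plan says.** - **Who is genotyped.** Under Genetic testing: "Participants assigned to the groups B and D will undergo genetic testing to evaluate their CVD genetic risk profile". Study procedure agrees: "Participants in Groups B and D will also undergo a salivary swab for PRS analysis". Those tested are then sorted into three groups: "individuals will be classified into three main genetic risk categories for CVD: High risk, Intermediate risk, and Normal risk".
- **What everyone has measured at baseline.** Study procedure describes questionnaires, a cardiovascular examination and blood tests ("Blood analysis will also be conducted, assessing parameters such as total cholesterol, HDL and LDL cholesterol, triglycerides", plus CRP and glycaemic measures). No genotyping or DNA storage is described for A or C.
- **Which arms are compared.** Statistical methods for primary and secondary outcomes: "Groups D, C, and B will be compared with group A". The Hypothesis section adds a comparison of the PRS arms with the arm given the smart band without PRS, which is C.
- **What the subgroup analysis is for.** Subgroup analyses lists "PRS levels (high, intermediate, normal" with the other factors and gives one aim for all of them: to "investigate whether the efficacy of the interventions varies across these identified participant subgroups". It sets no limit on the contrasts that PRS level may enter.
- **Moderation and mediation.** The same section sets out to "explore potential moderating and mediating effects based on participant characteristics". It names sociodemographic factors, genetics and baseline lifestyle as things that may do either.

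**The concern.** A randomised subgroup effect needs the subgroup variable in both arms of the contrast. Here the variable is a by-product of the intervention under test: people have a PRS level only if they were allocated to receive one.

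Whether feedback works differently after a high, intermediate or normal result is a natural question for this trial. A table headed by PRS level in a trial report would be read as randomised evidence on it, and the design cannot supply that evidence.

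A smaller point sits in the same section. A mediator lies on the path from allocation to outcome, so allocation must be able to change it. Age, gender, education, genotype and baseline lifestyle are fixed before allocation. They can moderate an effect but cannot mediate it.

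**Working it through.** **Inputs.** 255 per arm, 1,020 in total, 30% withdrawal, planning rates of 5% (A), 8% (B), 10% (C) and 15% (D), alpha 0.05 and 80% power (Sample size estimation). PRS is assayed in B and D only (Genetic testing, Study procedure).

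**Step 1: the plan's own figure.** A global four-group chi-square test (3 df) comes close to it.
- Mean rate = (0.05 + 0.08 + 0.10 + 0.15)/4 = 0.095.
- Sum of squared deviations = 0.002025 + 0.000225 + 0.000025 + 0.003025 = 0.0053.
- Effect size w² = (0.0053/4)/(0.095 × 0.905) = 0.0154.
- Required total is about 707, or 176.9 per arm. 176.9/0.70 = 252.7, so 253 per arm against the stated 255.
- Evaluable per arm: 255 × 0.70 = 178.5, taken as 178.

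The structural point below does not depend on this figure.

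**Step 2: where PRS level exists.** B and D: 2 × 255 = 510 of 1,020 (about 357 of 714 after withdrawal). A and C: 0 of 510.

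| Contrast | Source | PRS known in |
|---|---|---|
| B vs A | Statistical methods; Hypothesis | B only |
| C vs A | Statistical methods | neither |
| D vs A | Statistical methods; Hypothesis | D only |
| B vs C | Hypothesis | B only |
| D vs C | Hypothesis | D only |
| D vs B | not among the stated contrasts | both |

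**Step 3: why the gap cannot be filled.** Write μ(arm, k) for the mean outcome at PRS level k. The effect of B versus A at high PRS is μ(B, high) − μ(A, high). Arm A supplies only its overall mean μ(A), a weighted average of three unknown stratum means. Randomisation lets the weights be borrowed from B and D, but not the stratum means. The two obvious substitutes give:

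- One stratum against the whole arm: μ(B, high) − μ(A) = [μ(B, high) − μ(A, high)] + [μ(A, high) − μ(A)].
- High against normal within B: μ(B, high) − μ(B, normal) = [difference between the two disclosure effects] + [μ(A, high) − μ(A, normal)].

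In each, the last bracket is a difference between kinds of people, not an effect of allocation, and the trial has no data on it.

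**Step 4: what D versus B can deliver.** Two-sided 0.05, no continuity correction, 8% versus 15%, n per arm:

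z = [0.07√n − 1.96√(2 × 0.115 × 0.885)] / √(0.08 × 0.92 + 0.15 × 0.85) = (0.07√n − 0.884)/0.448

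- n = 178: z = (0.934 − 0.884)/0.448 = 0.11, power about 54%.
- 80% power would need 325 evaluable per arm, or 325/0.70 = 465 recruited.
- Within one PRS stratum, with the same two rates assumed to apply there. The protocol does not give stratum shares, so these are assumptions:

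| Assumed share | n per arm | Power |
|---|---|---|
| 10% | 18 | about 10% |
| 20% | 36 | about 15% |
| one third | 59 | about 22% |
| 50% | 89 | about 31% |

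**Step 5: mediators.** Study procedure re-administers the questionnaire, including psychological status, at T2 and T3. A measure taken after randomisation (T2) that precedes a later outcome (T3) is therefore already collected.

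**The case against.** The strongest reply is that the section names no contrast for the PRS subgroup. A reader might infer that high-PRS members of B or D will be set against all of A, but the protocol nowhere says so. Assigning each factor to its contrast is ordinary analysis-plan content, and that plan is not shown. This part stands: the biased comparison is a risk left open, not a stated analysis. It does not dispose of the point, because no later document can supply a PRS level that was never measured in A and C, while the section as written applies PRS level to the efficacy of the interventions without restriction.

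A reader might also go further and conclude that no PRS-level analysis is possible, or that the main results are compromised. Neither follows. D versus B remains randomised within PRS level. The whole-arm comparisons that address the primary objective do not use PRS level.

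Three further points are fair. The subgroup work is presented as exploratory, and PRS is one factor among many. The bias in Step 3 would vanish if PRS were unrelated to the outcome without disclosure; the protocol gives no figure either way, so its size cannot be calculated. The mediator point is largely one of terminology, since suitable data after randomisation are already collected.

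**Conclusion.** The point holds as a mismatch within the protocol. PRS level is offered as a modifier of intervention efficacy, yet all five contrasts named under Hypothesis and Statistical methods involve at least one arm without it, and 510 of 1,020 participants will never have it. This rests only on the protocol's description of who is tested, and would change only if A and C were genotyped under arrangements the article does not mention.

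The one usable contrast, D versus B, asks whether adding the app and band works differently by PRS level. It does not ask whether the effect of disclosure depends on the result disclosed. Its power is about 54% overall at the planning rates and about 10% to 31% within a stratum for assumed shares of 10% to 50%.

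Treating baseline characteristics as mediators is a separate, smaller error of wording. The matter should be corrected, but it does not touch randomisation, sample size or the primary intention-to-treat comparisons.

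**What to change.** In Subgroup analyses:

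1. Remove PRS level as an effect modifier for every contrast with A or C.
2. Keep it only for D versus B, with an interaction test, labelled exploratory. State that this contrast is additional to those named under Hypothesis and Statistical methods, that it tests the digital component and not disclosure, and that power is low.
3. Label changes by PRS level within B and D as observational.
4. Treat the listed baseline characteristics as moderators only. Take mediators from measures after randomisation, for example psychological status at T2 with T3 outcomes.

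This costs a change of wording and one added exploratory contrast; no new data are needed. The price is that the trial gives up any randomised claim on whether the effect of disclosure depends on PRS level. If the sponsor wants to keep that question, A and C would have to be genotyped too, with results withheld until follow-up ends. That means sampling up to 510 more people and is subject to consent and ethics approval.

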### Hypothesis

The hypothesis is that achieving the endpoints is more likely with at least one of these interventions (CVD PRS alone or in combination with digital technology) compared to individuals who only undergo the traditional CVD risk assessment at the beginning of the study, as well as compared to individuals who receive traditional risk assessment along with the use of smart band.

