## Study design

This is an RCT with four parallel arms, as illustrated in Figure 1. Participants will be randomly assigned to the following intervention groups:

A. No Intervention—Traditional CVD risk assessment.B. Traditional CVD risk assessment plus Genetic testing (CVD PRS).C. Traditional CVD risk assessment plus Digital intervention (use of an app and a smart band).D. Traditional CVD risk assessment plus Digital intervention (use of an app and a smart band) plus genetic testing (CVD PRS).

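### PRS level is listed as a modifier of intervention efficacy, but PRS is measured only in arms B and D, so no planned contrast with A or C can be formed within a PRS level

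*Protocol article*

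**What the plan says.** The Subgroup analyses section includes "PRS levels (high, intermediate, normal") in its list of factors. It gives the aim of the whole exercise as to "investigate whether the efficacy of the interventions varies across these identified participant subgroups", and it closes by naming genetics among the possible moderators or mediators.

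The measurement of PRS is restricted by arm:

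- Genetic testing section: "Participants assigned to the groups B and D will undergo genetic testing to evaluate their CVD genetic risk profile".
- Study procedure section: "Participants in Groups B and D will also undergo a salivary swab for PRS analysis".
- Study design section: arm A is "No Intervention—Traditional CVD risk assessment", and arm C adds only the app and smart band. The article describes no sampling, storage or later genotyping of DNA in A or C.

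The comparisons come from two places. The statistical methods section states that "Groups D, C, and B will be compared with group A". The Hypothesis section sets the PRS arms against A, "as well as compared to individuals who receive traditional risk assessment along with the use of smart band", which is arm C.

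**The concern.** A subgroup analysis of efficacy needs the subgroup variable in both arms of the contrast. The patient characteristics on the list, such as age, education and baseline lifestyle category, can be recorded in all four arms. PRS level exists only where the intervention under study was given, yet it is listed with the others without distinction.

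The trial's primary objective concerns the provision of PRS information. Readers will want to know whether the response depends on the result disclosed, and the subgroup section appears to promise an answer. If an analyst produces a PRS-level result against A from the available data, a difference between kinds of people could be read as a difference in efficacy.

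**Working it through.** **Inputs (protocol article).** Four arms of 255, total 1,020; withdrawal 30%; planned transition rates 5% (A), 8% (B), 10% (C), 15% (D), all from Sample size estimation. PRS is measured in B and D only. The article gives no distribution of participants over PRS levels, so any share below is an assumption.

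**The plan's own figure.** An overall four-group chi-square test (3 df, alpha 0.05, power 80%) comes close to the stated size. The mean rate is 9.5%. The sum of squared deviations is 0.045² + 0.015² + 0.005² + 0.055² = 0.0053, and 0.0053 / (0.095 × 0.905) = 0.0616 per participant per arm. This needs 177 per arm, and 177 / 0.70 gives 253, or 1,012 in total, against the stated 255 and 1,020. The point below does not depend on this calculation.

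**Who has a PRS level.** B and D: 2 × 255 = 510 randomised, about 357 after 30% loss. A and C: 2 × 255 = 510 with no PRS value.

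**Which contrasts can be formed within a PRS level.**

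| Contrast | Source | PRS known in both arms? |
|---|---|---|
| B vs A | statistical methods | no (A) |
| C vs A | statistical methods | no (A and C) |
| D vs A | statistical methods | no (A) |
| B vs C | hypothesis | no (C) |
| D vs C | hypothesis | no (C) |
| D vs B | not listed in the statistical methods | yes |

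The obstacle is one of identification, not of model choice. The effect of B at level k is p(B,k) − p(A,k). Randomisation makes the shares of the three levels the same in A as in B in expectation, but it does not show who in A belongs to which level. The only information on A is its overall rate, a share-weighted average of p(A,high), p(A,intermediate) and p(A,normal): one equation with three unknowns. The same holds for C.

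**What the collected data allow instead.**

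1. A PRS-level subset of B or D against all of A. A genetically selected group is set against an unselected one, so this is not a randomised comparison.
2. High against normal PRS within B or D. Different people are compared under the same allocation, so the result is an association and not an intervention effect.
3. D against B within a PRS level. This is randomised, because the germline score is fixed before allocation and measured in both arms. Both arms receive their PRS result, so it tests the addition of the app and smart band.

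**Precision of option 3.** Evaluable per arm: 255 × 0.70 = 178.5, taken as 178. Assume 20% at high PRS: about 36 per arm, leaving 142. Use 15% and 8% in both strata.

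- Binomial variance: 0.15 × 0.85 + 0.08 × 0.92 = 0.1275 + 0.0736 = 0.2011.
- SE in the high-PRS stratum: √(0.2011 / 36) = 0.075, or 7.5 points, against a planned D−B difference of 7 points.
- SE in the other 80%: √(0.2011 / 142) = 0.038.
- SE of the interaction: √(0.2011 / 36 + 0.2011 / 142) = 0.084, or 8.4 points.
- Power for D vs B (two-sided 0.05) is about 55% over all levels. Within a level holding 10%, 20%, 33% or 60% of participants it is about 10%, 15%, 22% or 36%.

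**The case against.** The strongest reply is that this is one entry in a long list of exploratory factors. The intention-to-treat comparisons and the sample size do not use PRS level. The stated objective and hypothesis concern the provision of PRS information overall, and neither mentions effects by level. This stands, and it limits the point to something that should be corrected, not a flaw in the primary analysis.

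A second reply is that the subgroup section names no contrast for the PRS factor. It does not say that high-PRS participants will be compared with all of A, and a look at D versus B, or at disclosed category within B and D, could fit its wording. This stands in part. The protocol does not commit to a biased comparison, so a reader should not infer that one is planned. The documents also give no basis for sizing a bias, since they offer no transition rate by PRS level. But the section does promise to compare efficacy across PRS levels, and every contrast that isolates PRS information has an ungenotyped comparator. A later analysis plan could not repair that, because the values are absent for whole arms. Reading the factor as a mediator does not help either: allocation does not alter a person's genotype.

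A reader might also infer that any PRS-level result from this trial would be non-randomised. That goes too far, because D versus B within a level is randomised.

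**Conclusion.** The point holds in limited form. The stated subgroup analysis conflicts with the stated data collection: PRS level is unknown by design in 510 of 1,020 participants, and 0 of 3 planned contrasts with A, and neither of the two with C, can be formed within a PRS level. This count rests only on the article's text and needs no numerical assumption.

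The one randomised PRS-level comparison, D versus B, answers a different question and answers it imprecisely. The figures of 7.5 and 8.4 points assume 178 evaluable per arm, a 20% high-PRS share and the planned rates of 15% and 8% in each stratum. Confidence in the conflict is high. The priority is should-fix, because the factor is exploratory and the primary and secondary analyses stand without it.

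**What to change.** Amend the Subgroup analyses section as follows:

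- Remove PRS level as a moderator of any contrast with A or C.
- Limit it to an exploratory interaction of D versus B with PRS level. Describe this as a test of the digital add-on among people who all receive their PRS result, and state its low precision.
- Label gradients across PRS levels within B or D as descriptive and non-randomised, with no efficacy claim.

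The cost is wording only, with no new samples. The downside is that the trial no longer claims to show how the effect of PRS disclosure varies by PRS level. Keeping that claim would require genotyping A and C with results withheld until after the final visit. That is a larger change, needing additional samples, consent and ethics approval.
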